### Evaluation of the Project 

The evaluation of educational interventions will aim to analyze and interpret relevant aspects of the multidimensional intervention. It will involve both the school team (teachers) and the recipients (children and families) participating in the LIVELY project and will be conducted at the end of the school year (T1).

The feasibility of the multidimensional educational intervention at school will be assessed in terms of satisfaction, learning, and organization. Three main areas of evaluation of educational interventions will be distinguished, namely, satisfaction (by children, families, and teachers), learning (by children), and organizational impact in the work context (by teachers).

The children's and their families' satisfaction will be assessed through an ad hoc questionnaire investigating the level of appreciation regarding the proposed activities. The children's knowledge of the topics covered in the lessons (healthy and sustainable nutrition and lifestyle) will be collected through age-appropriate questionnaires (true/false items, multiple-choice items, insertion) or short compositions, depending on their age group. This assessment will help us determine whether the concepts explained in the lessons have been learned and whether the educational model used is appropriate for the target population. The overall satisfaction and organizational impact of the interventions will be evaluated by teachers through an ad hoc structured questionnaire, which will explore the following issues: (1) usefulness (definition and consistency/congruence of the multidimensional interventions with the project objectives, (2) usefulness of the interventions and materials prepared), (3) didactics (competence and appropriateness of the teaching techniques of the study teams addressed to the subjects, support received by the study teams during the implementation of the activities), (4) organization, and (5) services (timing, facilities and appropriateness of the schools' premises). In addition, teachers will be asked to refer to the reproducibility of the intervention in other classrooms or schools. All items in the questionnaire will be rated on a Likert-type scale.

### Sample Size Calculation

This type of study did not require a sample size calculation, but we expected to enroll about 300 to 350 children aged between 6 and 12 years from 15 to 20 classes (in primary school and in the first class of secondary school) based on the availability/willingness of teachers to participate and the resources.

This would allow us to estimate the prevalence of overweight and obesity between 23% and 24%, with a 20% relative precision and within a 95% CI. These data are in line with those observed in the Okkio alla Salute 2019 survey in the Lombardy region [41].

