## Results

### Preliminary Results

Recruitment lasted throughout October 2023. Out of the 275 children from the 14 classes participating in the project, 227 whose parents approved and signed the informed consent were included in the study.

The mean age was 8.9 (SD 1.2) years, and 48% (n=110) were males. Children from the 14 classes were distributed as follows: 5.3% (n=12 children) from the second year (1 class), 33.9% (n=77 children) from the third year (5 classes), 15.9% (n=36 children) from the fourth year (2 classes), and 44.9% (n=102 children) from the fifth year (6 classes). No first-graders took part in the project. Data related to demographic data, including age, ethnicity, weight, height, BMI *z* score, and WHtR are shown for the total population and by sex in Table 3.

**Table 3 table3:** Demographic characteristics of the study population^a^.

Characteristics		Study population			*P* value	
		Total (n=227, 100%)	Male (n=110, 48%)	Females (n=117, 52%)		
Age (years), mean (SD)		8.9 (1.2)	8.9 (1.2)	8.9 (1.1)	0.975^b^	
Age range (years)		6-12	6-12	7-12		
**Place of birth, n (%)**						0.091^c^
	Italy	170 (79.3)	83 (75.5)	97 (82.9)		
	Europe	10 (4.4)	9 (8.2)	1 (0.9)		
	South America	11 (4.8)	6 (5.5)	5 (4.3)		
	Africa	23 (10.1)	10 (9.1)	13 (11.1)		
	Asia	3 (1.3)	2 (1.8)	1 (0.9)		
**Ethnicity, n (%)**						0.858^c^
	Caucasian	83 (36.6)	44 (40)	39 (33.3)		
	North African	80 (35.2)	35 (31.8)	45 (38.5)		
	Latin American	31 (13.7)	16 (14.5)	15 (12.8)		
	Asian	20 (8.8)	9 (8.2)	11 (9.4)		
	Black African	4 (1.8)	1 (0.9)	3 (2.6)		
	Mixed	9 (4)	5 (4.5)	4 (3.4)		
**Attended class, n (%)**						0.640^c^
	First-year class	0 (0)	0 (0)	0 (0)		
	Second-year class	12 (5.3)	8 (7.3)	4 (3.4)		
	Third-year class	77 (33.9)	36 (32.7)	41 (35)		
	Fourth-year class	36 (15.9)	17 (15.5)	19 (16.2)		
	Fifth-year class	102 (44.9)	49 (44.5)	53 (45.3)		

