**Anthropometric measurements, mean (SD)**						
	Weight (kg)	35.86 (10.53)	35.27 (10.5)	36.41 (10.57)	0.419^b^	
	Height (cm)	136.33 (8.74)	135.85 (8.38)	136.75 (99)	0.420^b^	
	Waist circumference (cm)	65.19 (11.37)	65.22 (10.95)	65.15 (11.79)	0.966^b^	
	Bicep circumference (cm)	22.11 (41)	21.72 (4.12)	22.47 (3.89)	0.159^b^	
	WHtR^d^	0.48 (07)	0.48 (07)	0.48 (07)	0.666^b^	
	BMI *z* score	0.87 (1.42)	0.87 (1.55)	0.87 (1.30)	0.971^b^	
**BMI z score classes, n (%)**						0.025^c^
	Underweight	5 (2.2)	4 (3.6)	1 (0.9)		
	Normal weight	169 (74.4)	80 (72.7)	89 (76.1)		
	Overweight	41 (18.1)	16 (14.5)	24 (21.4)		
	Obesity	12 (5.3)	10 (9.1)	3 (1.7)		
**Central obesity, n (%)**						0.329^c^
	WHtR <0.5	150 (66.1)	76 (69%)	74 (63%)		
	WHtR ≥0.5	77 (33.9)	34 (31%)	43 (37%)		

^a^Table shows the demographic and anthropometric characteristics of the overall study population and then divided between male and female students. Categorical variables are presented as n (%), and continuous variables are presented as mean (SD).

^b^*P* value of the *t* test between male and female students.

^c^*P* value of the chi-square test between male and female students.

^d^WHtR: waist-to-height ratio.

The percentage of normal weight, overweight, and obesity (defined by BMI *z* score) and central obesity (according to the WHtR cut-off) is reported in Table 4. Among the overall sample, 18.1% (n=41; 95% CI 13.7%-23.7%) were overweight, while 5.3% (n=12; 95% CI 3%-9%) were obese. Male students had a higher prevalence of obesity than female students (9.1% vs 1.7%, *P*=.03 respectively). Conversely, the overall prevalence of central obesity was similar between male and female students, respectively (31% vs 37%, *P*=.329).

**Table 4 table4:** Weight status prevalence according to BMI z score and its relation to WHtR^a^ in male and female students.

Participants				Total, n (%)		WHtR <0.5, n (%)		WHtR ≥0.5, n (%)
**Males**				110 (100)		76 (69)		34 (31)

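### The only precision stated for the primary prevalence objective, 20% relative, was not reached with the 227 children enrolled, and it makes no allowance for participation by class

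*Protocol article*

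**What the plan says.** The primary objective (Study Objectives) is the prevalence of overweight and obesity in primary school children, together with its determinants. The Sample Size Calculation section opens with "This type of study did not require a sample size calculation" and then sets an expectation: "we expected to enroll about 300 to 350 children aged between 6 and 12 years from 15 to 20 classes". The number rests on teachers' willingness and on resources. The section adds that this would allow the study to "estimate the prevalence of overweight and obesity between 23% and 24%, with a 20% relative precision", at 95% confidence. It mentions no design effect and no intraclass correlation.

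Recruitment ended in October 2023, and Preliminary Results gives its outcome as follows: "Out of the 275 children from the 14 classes participating in the project, 227 whose parents approved and signed the informed consent were included". Both the number of children and the number of classes are below the planned ranges. The text after Table 3 gives intervals for the two weight categories separately: "18.1% (n=41; 95% CI 13.7%-23.7%) were overweight, while 5.3% (n=12; 95% CI 3%-9%) were obese". The Discussion gives the combined prevalence by sex only (26 males, 24%; 27 females, 23%), without intervals. Neither the Discussion nor Study Limitations comments on the shortfall against the planned precision.

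**The concern.** The 20% figure is the only quantitative design property offered for the primary objective. It depends on an enrolment that the same article shows was not achieved. For combined overweight and obesity, the quantity the figure describes, the reader has no interval to set against it. The planning figure is therefore the only guide to precision, and it is too favourable.

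The calculation also treats children as independent. They entered through classes whose teachers agreed to take part, so children in one class may resemble each other in age, neighbourhood and background. Any positive correlation within classes widens the interval further.

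**Working it through.** **Inputs from the article.** Prevalence p = 0.23 to 0.24, read as overweight and obesity combined; relative precision r = 0.20; 95% two-sided, z = 1.96; planned N = 300 to 350 in 15 to 20 classes; enrolled N = 227 in 14 classes; observed 41 + 12 = 53 children with overweight or obesity. The sex-specific counts in Table 3 add to 40 and 13 rather than 41 and 12, but the combined total is 53 either way.

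**Step 1. Reproduce the planning statement.** Required n = z²(1−p)/(p·r²).
- p = 0.23: 3.8416 × 0.77 / (0.23 × 0.04) = 321.5, so 322.
- p = 0.24: 3.8416 × 0.76 / (0.24 × 0.04) = 304.1, so 305.

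Both lie inside 300 to 350, so the statement reproduces under simple random sampling.

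**Step 2. Precision at the enrolled size.** Relative half-width = z·√(p(1−p)/n)/p.
- p = 0.23, n = 227: half-width 0.0547, relative 23.8%.
- p = 0.24, n = 227: half-width 0.0556, relative 23.1%.
- Observed 53/227 = 23.3%: Wald 95% CI 17.8% to 28.9%, relative 23.6%; Wilson 95% CI 18.3% to 29.3%.

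The enrolled number is below the requirement by 1 − 227/305 = 26% (p = 0.24) to 1 − 227/322 = 30% (p = 0.23).

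**Step 3. Clustering at the enrolled size.** Design effect = 1 + (m−1)·ICC, with m = 227/14 = 16.2. The article gives no ICC, so the values below are assumptions. The relative half-width at p = 0.235 is 23.5% × √(design effect).

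| Assumed ICC | Design effect | Relative half-width at n = 227 |
|---|---|---|
| 0 | 1.00 | 23.5% |
| 0.01 | 1.15 | about 25% |
| 0.02 | 1.30 | about 27% |
| 0.05 | 1.76 | about 31% |

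**Step 4. Room for clustering in the plan itself.** At the top of the planned range, N = 350, the largest design effect that still gives 20% is 350/321.5 = 1.09 (p = 0.23) to 350/304.1 = 1.15 (p = 0.24).
- With 15 classes (m = 23.3) and p = 0.23, the largest ICC is 0.089/22.3 = 0.004.
- With 20 classes (m = 17.5) and p = 0.24, it is 0.151/16.5 = 0.009.
- At an assumed ICC of 0.01, N = 350 gives 20.1% (20 classes, p = 0.24) to 21.2% (15 classes, p = 0.23), a slight miss throughout.

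**The case against.** The planning sentence is conditional and prospective. It speaks of an expected enrolment, it reproduces under independence, and it never promises 20% at 227. The article reports the enrolment openly, and a planning rationale is normally left as written. All of this stands. It is a reason to keep the 20% figure as the planned value, but not to leave it without an achieved counterpart once the condition is known to have failed.

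A reader might infer that the sample size arithmetic is wrong because 300 children fall short. The documents do not support that. At 300 the relative half-width is 20.1% to 20.7%, a trivial miss at the lower end of an approximate range, and the required number lies inside that range.

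A reader might also infer that the article hides the precision of the separate overweight and obesity estimates, or fails a promise about them. It prints a 95% CI for each, calculated on the enrolled children, and it promises 20% only for the combined figure. What is missing is the interval for that combined figure and an allowance for class.

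The ICC values are assumed, so the clustered figures show sensitivity only and should not be printed as the study's achieved precision.

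Finally, if the target were only the 275 children in the participating classes, a finite-population correction would reduce the half-width to 23.5% × √(48/274), about 10%. The article states no such target or correction. Its objective concerns primary school children in general, and the 227 are those whose parents consented rather than a random draw from the 275.

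**Conclusion.** The point holds as a planned precision left standing after enrolment fell short. For the combined prevalence, the achieved relative precision is about 23-24%, or about ±5.5 percentage points, instead of 20%. That part needs only the article's own figures, the usual large-population formula and independent children. Clustering by class can be expected to make it worse by an amount the document does not allow one to compute. Assumed ICCs of 0.01 to 0.05 give about 25% to 31%, and even the top of the planned range would tolerate an ICC of only about 0.004 to 0.009. The planning arithmetic itself is sound under independence. The matter affects how the primary estimate should be read but does not invalidate the study.

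**What to change.** In Sample Size Calculation, keep the 20% figure but label it as the planned value for 300 to 350 independently sampled children, and add that it was not reached at 227. In Preliminary Results, report the combined prevalence, 53/227 = 23.3%, with its 95% CI (about 17.8% to 28.9% by the Wald method before clustering). Give as the main interval one that allows for class, either cluster-robust or using a design effect estimated from the study's own 14 classes. With so few classes, the estimated design effect will itself be imprecise, and the text should say so.

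The cost is a few sentences and one extra calculation on baseline data already collected. The stated precision becomes less favourable, and no additional children are needed.

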### Statistical Analysis

Descriptive analysis will be performed to summarize the baseline characteristics of the involved children according to normal weight, overweight, and obesity classifications. Descriptive data were expressed as counts (percentages) for categorical data and as means (SD) for continuous variables. The means for continuous variables were compared using independent group *t* tests when the data were normally distributed; othewise, the Mann-Whitney test was applied. Categorical variables were compared using the chi-square test. Main determinants of overweight/obesity among children will be investigated according to clinical conditions, dietary patterns, physical activity habits, and environmental and behavioral (family) conditions collected at the baseline using logistic/multinomial regression models.

Specifically, according to the questionnaire results and the information collected in the CRF, children will be identified as “fully adherent,” “partially adherent,” or “poorly adherent” to the WHO recommendations regarding eating and lifestyle habits [42].

The obesogenic environment will be investigated by summarizing all information collected with an appropriate index by assigning a score ranging from 0 (least obesogenic) to 100 (most obesogenic). Each item will be assigned a score from 0 to 1: variables that were considered positive aspects of the environment (grocery, stores/superstores, exercise opportunities) will be reverse scored so that a lower score for these variables indicates a healthier environment. Variables that are considered negative aspects (fast food restaurants, food budgets at home, using a car to go to school) will be scored as is, so a higher score indicates an unhealthy environment. The final index will be calculated by summing up the score for the single items and then normalized to lie between 0 and 100.

Indices for each dimension and an aggregate index will also be calculated to assess the level of satisfaction with the training intervention, learning and overall knowledge of the topic, and the intervention’s organization and reproducibility. Multivariate statistical analysis will be used to investigate general and specific quality dimensions and factors, and it will be correlated with the other aforementioned measures. Changes in dietary and lifestyle habits in the children, behavioral attitudes of their families, and the children's anthropometric measurements will be assessed at 6 (T1) and 12 months (T2) starting from baseline. All results will be stratified by sex and age groups.

## Results

### Preliminary Results

Recruitment lasted throughout October 2023. Out of the 275 children from the 14 classes participating in the project, 227 whose parents approved and signed the informed consent were included in the study.

The mean age was 8.9 (SD 1.2) years, and 48% (n=110) were males. Children from the 14 classes were distributed as follows: 5.3% (n=12 children) from the second year (1 class), 33.9% (n=77 children) from the third year (5 classes), 15.9% (n=36 children) from the fourth year (2 classes), and 44.9% (n=102 children) from the fifth year (6 classes). No first-graders took part in the project. Data related to demographic data, including age, ethnicity, weight, height, BMI *z* score, and WHtR are shown for the total population and by sex in Table 3.

**Table 3 table3:** Demographic characteristics of the study population^a^.

Characteristics		Study population			*P* value	
		Total (n=227, 100%)	Male (n=110, 48%)	Females (n=117, 52%)		
Age (years), mean (SD)		8.9 (1.2)	8.9 (1.2)	8.9 (1.1)	0.975^b^	
Age range (years)		6-12	6-12	7-12		
**Place of birth, n (%)**						0.091^c^
	Italy	170 (79.3)	83 (75.5)	97 (82.9)		
	Europe	10 (4.4)	9 (8.2)	1 (0.9)		
	South America	11 (4.8)	6 (5.5)	5 (4.3)		
	Africa	23 (10.1)	10 (9.1)	13 (11.1)		
	Asia	3 (1.3)	2 (1.8)	1 (0.9)		
**Ethnicity, n (%)**						0.858^c^
	Caucasian	83 (36.6)	44 (40)	39 (33.3)		
	North African	80 (35.2)	35 (31.8)	45 (38.5)		
	Latin American	31 (13.7)	16 (14.5)	15 (12.8)		
	Asian	20 (8.8)	9 (8.2)	11 (9.4)		
	Black African	4 (1.8)	1 (0.9)	3 (2.6)		
	Mixed	9 (4)	5 (4.5)	4 (3.4)		
**Attended class, n (%)**						0.640^c^
	First-year class	0 (0)	0 (0)	0 (0)		
	Second-year class	12 (5.3)	8 (7.3)	4 (3.4)		
	Third-year class	77 (33.9)	36 (32.7)	41 (35)		
	Fourth-year class	36 (15.9)	17 (15.5)	19 (16.2)		
	Fifth-year class	102 (44.9)	49 (44.5)	53 (45.3)		
**Anthropometric measurements, mean (SD)**						
	Weight (kg)	35.86 (10.53)	35.27 (10.5)	36.41 (10.57)	0.419^b^	
	Height (cm)	136.33 (8.74)	135.85 (8.38)	136.75 (99)	0.420^b^	
	Waist circumference (cm)	65.19 (11.37)	65.22 (10.95)	65.15 (11.79)	0.966^b^	
	Bicep circumference (cm)	22.11 (41)	21.72 (4.12)	22.47 (3.89)	0.159^b^	
	WHtR^d^	0.48 (07)	0.48 (07)	0.48 (07)	0.666^b^	
	BMI *z* score	0.87 (1.42)	0.87 (1.55)	0.87 (1.30)	0.971^b^	
**BMI z score classes, n (%)**						0.025^c^
	Underweight	5 (2.2)	4 (3.6)	1 (0.9)		
	Normal weight	169 (74.4)	80 (72.7)	89 (76.1)		
	Overweight	41 (18.1)	16 (14.5)	24 (21.4)		
	Obesity	12 (5.3)	10 (9.1)	3 (1.7)		
**Central obesity, n (%)**						0.329^c^
	WHtR <0.5	150 (66.1)	76 (69%)	74 (63%)		
	WHtR ≥0.5	77 (33.9)	34 (31%)	43 (37%)		

^a^Table shows the demographic and anthropometric characteristics of the overall study population and then divided between male and female students. Categorical variables are presented as n (%), and continuous variables are presented as mean (SD).

^b^*P* value of the *t* test between male and female students.

^c^*P* value of the chi-square test between male and female students.

^d^WHtR: waist-to-height ratio.

The percentage of normal weight, overweight, and obesity (defined by BMI *z* score) and central obesity (according to the WHtR cut-off) is reported in Table 4. Among the overall sample, 18.1% (n=41; 95% CI 13.7%-23.7%) were overweight, while 5.3% (n=12; 95% CI 3%-9%) were obese. Male students had a higher prevalence of obesity than female students (9.1% vs 1.7%, *P*=.03 respectively). Conversely, the overall prevalence of central obesity was similar between male and female students, respectively (31% vs 37%, *P*=.329).

**Table 4 table4:** Weight status prevalence according to BMI z score and its relation to WHtR^a^ in male and female students.

Participants				Total, n (%)		WHtR <0.5, n (%)		WHtR ≥0.5, n (%)
**Males**				110 (100)		76 (69)		34 (31)
	**BMI *z* score (WHO^b^)**							
		Underweight	4 (3.6)		4 (5.3)		0 (0)	
		Normal weight	80 (72.7)		71 (93.4)		9 (26.5)	
		Overweight	16 (14.5)		1 (1.3)		15 (44.1)	
		Obesity	10 (9.1)		0 (0)		10 (29.4)	
**Females**				117 (100)		74 (63)		43 (37)
	**BMI** * **z** * **score (WHO)**							
		Underweight	1 (0.9)		1 (1.4)		0 (0)	
		Normal weight	89 (76.1)		71 (95.9)		18 (41.9)	
		Overweight	24 (21.4)		2 (2.7)		23 (53.5)	
		Obesity	3 (1.7)		0 (0)		2 (4.7)	

^a^WHtR: waist-to-height ratio.

**^b^**WHO: World Health Organization.

The second data collection was completed in June 2024 (T1), and the last data collection will be completed by the end of October 2024 (T2). Data analysis and a presentation of the complete results will be available after the end of 2024. 

## Discussion

### Overview

The rising prevalence of obesity worldwide represents a growing burden of noncommunicable diseases (NCDs) and a significant public health issue due to increasing public service health costs [13,18,43]. To prevent the early onset of NCDs in younger populations, additional policies, treatments, and financial investments must be made to contrast the growing pandemic of childhood obesity [44-46]. Based on scientific research [15], preventing childhood obesity requires a multifaceted approach including multiple areas of intervention. Therefore, it is essential to develop and carry out integrated programs that could cover a variety of topics (nutrition, physical activity, sleep hygiene, etc) at various levels (individual, family, school, and institutional) [47].

The LIVELY study enrolled 227 school-age children attending an elementary school in a multiethnic neighborhood in north Milan, Italy. Classes from the second to the fifth grade were included. No first-grade class joined the project because the availability of children to follow the lesson could not be optimal. This was because, during the first year of elementary school, children were just beginning to learn how to read and write, leading primary school teachers to abstain from participating in the project.

In line with previous studies [24-26], our preliminary results showed a high prevalence of overweight/obesity among the enrolled children, at 24% (n=26) for the male students and 23% (n=27) for the female students, with a higher prevalence of obesity among males (*P*=.007). Interestingly, the prevalence of central obesity was similar between the 2 sexes (*P*=.329).

### Study Strengths

A child's diet and physical activity can be significantly influenced by their surroundings, particularly family and school [48]. To date, many programs have been developed to prevent obesity in children, but the overall impact of these is questionable and does not include long-term follow-up measurements [24-26]. Thus, the LIVELY study has significant strengths. First, interventions involving different actors (children, families, teachers) and multidisciplinary professional expertise will be implemented, allowing us to address the different determinants of childhood obesity. Second, frontal lectures and games relating to the subject matter will be adapted to all age groups, dividing the children into 2 groups—first and second graders in one group, and third to fifth graders in the other. The strong multicultural component of the sample will be considered by involving them in stimulating and bonding activities. Third, an interactive digital lab will be developed to maximize learning outcomes by taking advantage of the children’s digital skills. Fourth, attention will be given to the opinions of all participants (children, parents, and teachers) to assess the feasibility and reproducibility of the project.

